### Sample size calculation

The sample size was determined to achieve 90% power to declare non-inferiority of magnesium hydroxide in case the proportion of patients with a score < 30 on the BFI at day 14 to be equal for magnesium hydroxide and macrogol/electrolytes assuming one-sided testing at a significance level of 2.5% [30]. The sample size was based on two non-randomized studies that showed that approximately 40% of patients starting with opioids and not using laxatives do not develop constipation after 14 days [31, 32]. Prophylaxis with laxatives can only be effective in (part of) the remaining 60% of patients. Treatment with macrogol/elektrolytes is effective in 70% of patients with symptomatic chronic constipation [33, 34]. Based on these data, we estimated the percentage of patients without constipation (BFI < 30) after 14 days of treatment with macrogol/electrolytes to be 82% (40% plus 0,7 × 60%). The main considerations are that the proportion of patients with a BFI < 30 under magnesium hydroxide at the non-inferiority margin should clearly be higher than the estimated 40% of patients without opioid induced constipation and the clinical judgement that more than 15% difference could no longer be translated in a conclusion that magnesium hydroxide is non inferior to macrogol/electrolytes. Based on the previous data, we calculated a sample size of 138 evaluable patients per arm. We will increase the inclusion with approximately 20% to anticipate potential loss to follow-up to N = 165 per arm.

### Statistical analysis

All data will be coded and collected in a secure cloud-based clinical data management platform (Castor EDC). Analysis will be performed using the latest version of IBM SPSS Statistics.

Primary analysis for non-inferiority will be performed both on a protocol and intention-to-treat basis. The primary outcome is the difference in proportion of responders (BFI < 30 at day 14) between the two arms. The primary analysis will use the Newcombe score method to estimate a one-sided 97.5% confidence interval for the difference in proportion of responders (proportion responders under magnesium hydroxide minus proportion responder under macrogol/electrolytes). The null hypothesis (H0: Magnesium hydroxide is inferior to macrogol/electrolytes in the prevention of OIC) will be rejected and non-inferiority will be claimed for magnesium hydroxide if the lower boundary of the 97.5% confidence interval is larger than the prespecified non-inferiority margin of -15%. An additional analysis will be performed in which the risk difference for response is estimated using a generalized linear model for a binomial outcome and an identity link, while adjusting for the stratification factors of center and constipation at the start of the study.

An additional per protocol analysis will be performed using inverse-probability-of-treatment-weighing (IPTW) in the intention-to-treat population. For this IPTW analysis, logistic regression analysis in the intention-to-treat population will be used to predict the probability of a subject being adherent based on predefined confounders. In this analysis, non-adherence is defined as < 80% of the prescribed laxative being taken as determined from the patient diary [35]. The inverse of the predicted probabilities will then be used as weights in an analysis comparing treatment outcomes between the groups and to estimate a per-protocol effect. In this weighted analysis, the risk difference for response and its two sided 95% confidence interval is estimated using generalized linear models for a binomial outcome and an identity link, while adjusting for the stratification factors.

Secondary analyses include the same analyses for constipation judged by professional care givers, based on the Rome IV criteria for opioid-induced constipation. Furthermore, we aim to study baseline predictors of the response to macrogol/electrolytes and magnesium hydroxide in patients starting with opioids, including sex, age, performance status and comorbidity.

Lastly, the cost-effectiveness of macrogol/electrolyte compared to magnesium hydroxide will also be a secondary outcome. The cost-effectiveness will primarily be influenced by the effect of the medication on healthcare resource use and quality of life, since their unit costs are similar. In this analysis, we will compare the cost-effectiveness of macrogol/electrolyte and magnesium hydroxide in patients. The analysis will be performed from a healthcare perspective with a time horizon of two weeks. A decision tree will be developed with branches for initial therapy and responders and non-responders. The costs and quality of life of the patients in the trial will be used as input for this decision tree. This requires data collection on healthcare procedures and quality of life in responders, non-responders and patients with side-effects of laxatives for the follow-up period of the study (two weeks). These healthcare procedures will be extracted from the modified iMCQ after two weeks. The modified iMCQ will be adjusted in such a way that resource use due to gastrointestinal complaints will only be measured in these patients with intensive healthcare resource use. All individual health care procedures will be linked to their unit costs. Reimbursement prices issued by the Dutch Healthcare Authority (NZa) and national reference prices will be used for this assessment as outlined in current Dutch pharmaco-economic guidance. Quality of life will be measured using the EQ-5D-5L at baseline and after two weeks.

A scenario will be added to the analyses for the use of naloxegol and naldemedine as a first-line treatment in case of OIC. Naloxegol and naldemedine are peripheral µ-receptor antagonists that have shown to be effective for the treatment of OIC [36]. There are no studies available yet evaluating the efficacy of naloxegol for prevention of OIC. For naldemedine there is one recent randomized controlled trial available that has evaluated the efficacy of naldemedine for prevention of OIC [10]. As no effect data of first-line treatment with naloxegol or naldemedine will be measured during the trial, the scenario analysis will be an early health-economic analysis. In this analysis we will use effect data based on literature and expert opinion and will perform a threshold analysis to estimate the effect size needed to result in a cost-effective intervention. Bootstrapping will be performed to assess the uncertainty of costs and utility loss of (sub)groups, while deterministic (one-way) and probabilistic sensitivity analyses will be performed to assess the uncertainty of the analyses in the decision tree.

With regards to missing data, we do not plan imputation for the main outcome. If unexpectedly outcomes are missing, we will perform sensitivity analyses using single-value imputation under the most extremes scenarios. Multiple imputation may be considered if important confounders are missing or if missing on the main outcome is higher than currently anticipated.

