### Treatment

Patients will be treated with either macrogol/electrolytes or magnesium hydroxide in a standard dosing regimen. Macrogol/electrolytes is started at a dose of 1 sachet (containing 13,125 g of macrogol) once daily and magnesium hydroxide at a dose of 724 mg t.i.d., both orally. Macrogol/electrolytes is regarded as the standard treatment (usual care) to which magnesium hydroxide will be compared. The dose of macrogol/electrolytes and magnesium hydroxide may be increased to 2 sachets daily or 1448 mg t.i.d., respectively, or may be decreased or discontinued because of intolerance or side effects during the study period. To determine whether a change of the dosage is needed, a contact moment with the local investigator by telephone will take place on day 7.

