### Study measurements

Demographic and baseline data will be extracted from the medical record. This includes sex, age, performance status, comorbidities, treatment with systemic and/or radiotherapy during the study period and the type and dose (converted to morphine equivalents) of the opioid which the patient will use.

The primary outcome measure is the proportion of patients with a score of < 30 on the Bowel Function Index (BFI), measured on day 14. The BFI is a clinician-administered, patient-reported questionnaire to assess clinically significant constipation, validated in patients receiving opioids for chronic non-malignant and malignant pain [20–22]. The BFI consists of three questions, assessing ease of defecation, feeling of incomplete bowel evacuation and personal judgement of the patient regarding constipation, each during the last 7 days and each rated on a scale of 0 (best possible outcome) to 100 (worst possible outcome). A total score ≥ 30 (mean of the three separate scores) indicates clinically significant constipation. A change of the total score of > 12 is regarded as clinically meaningful. The BFI has been used in a large ‘real world’ observational study in cancer patients receiving opioids [1] and in randomized trials of opioid antagonists for OIC [23–26]. It has been recommended as the assessment tool of choice for OIC [7, 27]. The BFI will be administered by the local investigator on day 0 (at the start of the study, after giving informed consent and before the randomization) and by telephone on day 14.

As a secondary outcome measure, the local investigator will assess the Rome IV criteria for opioid-induced constipation on day 0 and by telephone on day 14 (see Table 1). At least two of the six criteria have to be fulfilled in order to diagnose constipation.

Another secondary outcome measure is the 5-level EuroQol-5 Dimension questionnaire (EQ-5D-5L) completed on day 0 and 14. The EQ-5D-5L is a self-administered, generic assessment tool developed by the EuroQol Group to assess the quality of life and to determine cost-effectiveness. This measurement tool consists of five questions on dimensions of health (i.e., mobility, self-care, pain/discomfort, usual activities, and anxiety/depression) [28].

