Other secondary outcome measures include a pain score (Numeric Rating Scale, ranging from 0 to 10, on days 0 and 14), a questionnaire about patient satisfaction with the laxative on day 14 (one question on a four-point Likert scale, ranging from unsatisfied to very satisfied), a questionnaire about side effects of the laxatives on day 14 and a questionnaire about medical consumption (the modified iMTA Medical Consumption Questionnaire (iMCQ)) on day 14 [29]. An overview of the measurement tools can be found in Table 1.

Lastly, patients will report daily laxative use in a medication diary to evaluate protocol adherence and also daily use of escape medication.

**Table 1 Tab1:** Overview of measurement tools

Measurement tool	
Bowel Function Index (Day 0 and day 14)	3 questions about defecation, rated on a scale of 0 (best possible outcome) to 100 (worst possible outcome). Total score ≥ 30 (mean of the three separate scores) indicates clinically significant constipation. A change of the total score of > 12 is regarded as clinically meaningful.
Rome IV criteria for opioid-induced constipation (Day 0 and day 14)	At least two of the following criteria have to be fulfilled in order to diagnose constipation: - Straining > 25% of defecations - Lumpy or hard stools in > 25% of defecations - Sensation of incomplete evacuation in > 25% of defecations - Sensation of anorectal obstruction/blockage in > 25% of defecations - Manual manoeuvres to facilitate > 25% of defecations - < 3 spontaneous defecations per week
EQ-5D-5L questionnaire (Day 0 and day 14)	5 questions on dimension of health: mobility, self-care, pain/discomfort, usual activities, and anxiety/depression. Each dimension consists of 5 levels: no problems, slight problems, moderate problems, severe problems and extreme problems
Pain (Day 0 and day 14)	Numeric rating scale (0 = no pain, 10 = worst pain imaginable) Satisfaction with laxatives will be scored on a four-point Likert scale, ranging from unsatisfied to very satisfied Side effects of laxatives (i.e. bad taste, flatulence and nausea) will be scored on a four-point Likert scale (not at all, a bit, rather, very much)
Patient satisfaction (Day 14)	
Side effects (Day 14)	
Modified iMCQ (Day 14)	9 questions related to frequent occurring contact with healthcare providers. Each answer is dichotomous (yes/no) with the option to add the number of visits if the answer ‘yes’ is filled in.

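### The responder rule ignores escape medication, so a prevention failure rescued to BFI below 30 counts as a success; if rescue follows need in both arms, this favours non-inferiority

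*Protocol article*

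**What the plan says.** All references are to the protocol article.

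- **Responder rule** (Statistical analysis): "The primary outcome is the difference in proportion of responders (BFI < 30 at day 14) between the two arms". The Abstract and Study measurements give the same rule, and none of the three places adds a condition on other laxatives.
- **Recall period** (Study measurements): the three BFI items are scored "each during the last 7 days and each rated on a scale of 0 (best possible outcome) to 100 (worst possible outcome"). The day-14 score therefore describes roughly the second week of treatment.
- **Escape medication** (Study measurements): "patients will report daily laxative use in a medication diary to evaluate protocol adherence and also daily use of escape medication". The Abstract lists it among the things to be assessed. Statistical analysis does not mention it.
- **Stopping** (Treatment): the dose of either laxative "may be decreased or discontinued because of intolerance or side effects during the study period".
- **Analysis sets** (Statistical analysis): "Primary analysis for non-inferiority will be performed both on a protocol and intention-to-treat basis". A further weighted per-protocol analysis is planned, in which "non-adherence is defined as < 80% of the prescribed laxative being taken as determined from the patient diary".
- **Decision** (Statistical analysis): non-inferiority is claimed if "the lower boundary of the 97.5% confidence interval is larger than the prespecified non-inferiority margin of -15" percentage points, using the Newcombe score method.

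**The concern.** The trial asks whether one laxative prevents opioid-induced constipation about as well as another. A patient who became constipated on the allocated laxative, took something else, and scored below 30 on day 14 is a failure of prevention. The stated rule calls that patient a responder.

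The adherence rule does not catch this. It counts only how much of the allocated laxative was taken, so a patient who took all of it and also used escape medication is fully adherent and a responder, even in the weighted per-protocol analysis.

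In a superiority trial, such dilution usually works against the claim. In a non-inferiority trial it can work for it: the less effective laxative leaves more failures to rescue, and each rescued failure closes part of the gap. A claim of non-inferiority could then partly reflect the escape medication rather than the laxative under test.

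**Working it through.** **Inputs from the article.** Control response 82%, margin 15 points, 90% power and 138 evaluable per arm (Sample size calculation, "assuming one-sided testing at a significance level of 2.5"%); Newcombe interval (Statistical analysis); 1:1 allocation (Randomization, blinding and treatment allocation).

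**Input not in the article.** The fraction *r* of failures on the allocated laxative that escape medication brings to BFI < 30. No rate is given, so *r* is an assumption and is shown as a range.

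**Step 1. Reproduce the sample size.** n = 2 × 0.82 × 0.18 × (1.960 + 1.282)² / 0.15² = 137.86, rounded up to 138, as stated. Exact binomial enumeration of the Newcombe rule at 138 per arm gives 90.2% power when both rates are 82%. The sample size is not in error.

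**Step 2. Decision rule.** With observed proportions p_M (magnesium hydroxide) and p_C (macrogol/electrolytes), Wilson lower limit l_M and Wilson upper limit u_C, each at z = 1.960:

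L = (p_M − p_C) − √[(p_M − l_M)² + (u_C − p_C)²]; claim non-inferiority if L > −0.15.

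**Step 3. Equal conversion in both arms.** Put laxative-alone response exactly at the margin: 82% v 67%. After conversion, p_C = 0.82 + 0.18r and p_M = 0.67 + 0.33r, so the gap is 0.15 × (1 − r). Exact probability of a claim at 138 per arm:

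| r | p_C | p_M | gap (points) | claim probability |
|---|---|---|---|---|
| 0 | 82.0% | 67.0% | 15.0 | 2.7% |
| 10% | 83.8% | 70.3% | 13.5 | 5.2% |
| 20% | 85.6% | 73.6% | 12.0 | 9.6% |
| 30% | 87.4% | 76.9% | 10.5 | 17.1% |

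**Step 4. What if the 82% already includes rescue?** Hold p_C at 82% after rescue. Control response on the laxative alone is then (0.82 − r)/(1 − r), which is 80.0%, 77.5% or 74.3% for r = 10%, 20% or 30%. With a 15-point laxative-alone difference, p_M = 0.82 − 0.15(1 − r) = 68.5%, 70.0% or 71.5%. Claim probabilities are 5.1%, 9.0% and 15.0%, so the result hardly depends on this choice.

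**Step 5. Unequal conversion.** With fractions r_C and r_M, the gap is 0.15 + 0.18 r_C − 0.33 r_M. It shrinks unless r_C is at least 0.33/0.18 = 1.83 times r_M. At the extremes with 20% conversion in one arm only, the claim probability is 27.3% if only magnesium hydroxide failures are rescued and 0.4% if only macrogol failures are.

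**Step 6. Power if escape users count as non-responders.** If 5, 10 or 15 points of response are lost in both arms, the common rate is 77%, 72% or 67%. Power at 138 per arm is 84.8%, 80.2% or 76.5%. The formula in step 1 would then need 166, 189 or 207 per arm for 90%.

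**The case against.** The best defence is that a treatment-policy comparison is legitimate. Both laxatives are in current use, one arm is called usual care, and cost-effectiveness is an aim, so the outcome under each strategy, rescue included, is a sensible question. This stands, and it is why the present outcome can remain primary.

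Four stronger readings are tempting, but the article does not support them.

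- *The test does not hold its error rate.* A reader might infer this from step 3. For the hypothesis as written, about BFI < 30 at day 14 whatever produced it, the error at the margin is 2.7%. The higher figures apply only when the result is read as a statement about the laxative itself.
- *Rescue is unrestricted.* The article does not say which escape medication is allowed, or when. It is a condensed account, and the full protocol may set rules.
- *Patients who stop the allocated laxative are counted as successes throughout.* This is true only of the intention-to-treat analysis. The per-protocol and weighted analyses partly address stopping, by exclusion or reweighting. They are not described as addressing escape use.
- *The bias must favour magnesium hydroxide.* Step 5 shows that the direction is conditional. Attenuation is what to expect when rescue follows need, but open-label rescue decisions need not be equal between arms.

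Two further points stand. The 7-day recall can work against conversion, because a patient constipated enough to need rescue in that week may still report it and score 30 or more; *r* could therefore be small. A composite outcome has its own weakness: escape use is decided with the allocation known.

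**Conclusion.** The concern holds in a limited form. The responder rule is stated in full and takes no account of escape medication, although the diary records it daily and the BFI window lets it act on the score. The adherence rule leaves the same gap. The analysis is valid for the treatment-policy question, but it does not by itself support a conclusion about prevention by the laxative.

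The size cannot be fixed from the article. Assuming equal conversion and a laxative-alone difference exactly at the margin, 10% conversion about doubles the chance of a claim (2.7% to 5.2%) and 30% raises it to 17.1%. Both the size and the direction rest on those assumptions. The remedy is a prespecified companion analysis; the documents do not support replacing the primary outcome of a trial that began recruiting in October 2022.

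**What to change.** Keep BFI < 30 at day 14 as the primary outcome and label it a treatment-policy comparison. Before the data are analysed, add the following:

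1. A key sensitivity analysis in which a responder has BFI < 30 at day 14 **and** took no escape laxative and made no switch to another laxative in the 7-day BFI window, as recorded in the diary. Use the same Newcombe method and read the result against the same −15% limit.
2. A rule for missing diary days in that window.
3. A report of escape use by arm, so that readers can judge whether rescue was balanced.
4. A statement that the result will not be presented as non-inferiority of the laxative itself in preventing opioid-induced constipation unless this analysis agrees.

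Patient care and data collection do not change. The costs are reliance on complete diaries and on open-label rescue decisions, and lower power: about 85%, 80% or 76% at 138 per arm if 5, 10 or 15 points of response are lost in both arms. Failure of the sensitivity analysis alone should therefore be read as inconclusive rather than as evidence of inferiority.

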### Randomization, blinding and treatment allocation

Patients will be randomized after fulfilling eligibility criteria and written informed consent. The randomization will be 1:1 using computerized block randomization with varying block sizes of 2 and 4 in random order. Randomization will be stratified by center and presence of constipation at the start of the study, defined as a score ≥ 30 on the Bowel Function Index (BFI, see paragraph ‘study measurements’). Randomization will be performed by the local researcher after baseline assessments.

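### The deciding Newcombe interval is unstratified although randomisation is stratified by baseline constipation, and the responder rate behind a prevention claim also counts constipation that resolves

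*Protocol article*

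**What the plan says.** All references are to the Protocol article.

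- **Randomization, blinding and treatment allocation:** "Randomization will be stratified by center and presence of constipation at the start of the study", where constipation means a BFI of 30 or more. Under Study measurements, the BFI is taken on day 0, before randomisation.
- **Study population:** laxative use in the previous four weeks is an exclusion. A baseline BFI of 30 or more is not, so patients already constipated can enter.
- **Statistical analysis, primary:** "The primary analysis will use the Newcombe score method to estimate a one-sided 97.5% confidence interval for the difference in proportion of responders". Non-inferiority is claimed if the lower bound is "larger than the prespecified non-inferiority margin of -15" per cent. A responder is any patient with BFI below 30 on day 14. The null hypothesis is worded as inferiority in preventing OIC.
- **Statistical analysis, supporting:** "An additional analysis will be performed in which the risk difference for response is estimated using a generalized linear model for a binomial outcome", with an identity link and adjustment for centre and baseline constipation. The weighted per-protocol analysis uses the same link and adjustment.
- **Sample size calculation:** "The sample size was determined to achieve 90% power to declare non-inferiority of magnesium hydroxide", "assuming one-sided testing at a significance level of 2.5" per cent, with the two proportions taken "to be equal for magnesium hydroxide and macrogol/electrolytes" and the response "after 14 days of treatment with macrogol/electrolytes to be 82" per cent. The 82% starts from the share of patients who do not develop constipation without laxatives.

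**The concern.** There are three linked issues.

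1. **Precision.** Baseline constipation is the day-0 version of the outcome and plausibly prognostic. Stratified randomisation balances it between arms, but a crude interval does not credit that balance and overstates the uncertainty.

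2. **Meaning.** A patient with BFI of 30 or more on day 0 and below 30 on day 14 has had existing constipation resolved, not prevented. That patient enters the same proportion as one who never became constipated, and the result is read as a statement on prevention. If the laxatives differ in one stratum only, the pooled figure does not show the difference in the group the claim is about.

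3. **The adjusted model.** The analysis that does use the strata has an identity link and terms for eleven centres. With response near 80%, fitted risks can reach 1 and the fit can fail.

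**Working it through.** **Inputs from the protocol:** response 82% in both arms, margin 15 points, one-sided 2.5%, power 90%, 138 evaluable per arm, eleven centres.

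**Assumed, because the protocol gives neither:** the share q constipated at entry, and the gap g in response between the two strata.

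**Step 1: the plan's own figure.** n = 2 × 0.82 × 0.18 × (1.96 + 1.2816)² / 0.15² = 137.86, so 138 per arm, as stated. Exact enumeration of the Newcombe rule at 138 per arm gives power of 90.2%, and a one-sided error of 2.67% at 67% versus 82% when baseline prognosis is ignored. The sample size fits the unstratified analysis.

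**Step 2: width of the interval.** Hold overall response at 82%. Response is p0 = 0.82 + q·g in patients not constipated at entry and p1 = p0 − g in those constipated.

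- Crude variance per patient: V = 0.82 × 0.18 = 0.1476. SE = √(2 × 0.1476/138) = 0.04625, half-width 9.07 points.
- Within-stratum variance: W = (1 − q)·p0(1 − p0) + q·p1(1 − p1).
- The crude interval is too wide by a factor √(V/W).

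Example, q = 0.3 and g = 0.2: W = 0.7 × 0.88 × 0.12 + 0.3 × 0.68 × 0.32 = 0.1392. SE = √(2 × 0.1392/138) = 0.0449, half-width 8.80 points, excess 9.07/8.80 − 1 = 3%.

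**Step 3: power.** With s = √(2W/138), the crude rule has power Φ((0.15 − 0.0907)/s) and the stratified rule Φ(0.15/s − 1.96). For q = 0.3:

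| Gap (points) | p0 / p1 (%) | W | Stratified half-width | Crude too wide by | Power, crude v stratified |
|---|---|---|---|---|---|
| 10 | 85 / 75 | 0.1455 | 9.00 | 0.7% | 90.2 v 90.4% |
| 20 | 88 / 68 | 0.1392 | 8.80 | 3% | 90.7 v 91.6% |
| 30 | 91 / 61 | 0.1287 | 8.46 | 7% | 91.5 v 93.5% |
| 40 | 94 / 54 | 0.1140 | 7.97 | 14% | 92.8 v 95.8% |

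Simulation (200,000 runs per scenario, balanced within strata) agrees: 90.9 v 91.9%, 92.0 v 93.9% and 93.1 v 96.0% for gaps of 20, 30 and 40 points. The simulated one-sided error of the crude Newcombe rule is 2.37%, 2.09% and 1.63%. A simple stratified Wald interval gives 2.60%, 2.67% and 2.74%, close to the 2.67% in Step 1.

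**Step 4: mixing.** If the arms differ by d only among patients not constipated at entry, the pooled difference is (1 − q)·d. A pooled −15 points then corresponds to d = −15/(1 − q): −16.7 at q = 0.1, −21.4 at q = 0.3 and −30 at q = 0.5. If they differ only among patients constipated at entry, the pooled figure shows a difference although prevention is equal.

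**Step 5: identity-link model.** Simulations assumed eleven equal centres of 26 patients, response 87% and 65% by stratum with 30% constipated (0.7 × 87 + 0.3 × 65 = 80.4% overall), and a between-centre SD of 0 or 5 points. Across repeated runs, 13 to 19% of fits did not converge. Fits that failed or reached a fitted risk of 1 made up between 52 and 87%, depending on the implementation and the definition used. With baseline constipation as the only covariate every fit converged, so the centre terms cause the problem.

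**The case against.** **The plan does not ignore stratification.** An analysis adjusted for both factors is prespecified in the same paragraph. This stands: the issue is which analysis decides, not whether adjustment is planned.

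**The crude Newcombe interval is valid, on the scale of the margin and matched to the sample size.** This stands. Where baseline constipation is prognostic, its error is on the safe side for a non-inferiority claim.

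**The size rests on assumed inputs.** This stands. The nearest figure in the protocol is the 70% effectiveness of macrogol/electrolytes in chronic constipation, against 82% overall. Read as a 12-point gap with 30% constipated, it makes the interval only about 1% too wide.

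**A reader might infer that the trial falls short of its power.** With 90% and 50% response by stratum and 30% constipated, power is about 88% crude against 92% stratified. But overall response there is 0.7 × 90 + 0.3 × 50 = 78%, and at 78% the usual calculation ignoring strata gives only 85.3%. The figure below 90% comes from the lower response. At the planned 82%, every scenario examined stays at or above 90%.

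**A reader might also infer that the 82% leaves out patients constipated at entry, or that no result by stratum will ever be given.** The documents show neither. The cited cohorts are not available to check, results by stratum may sit in an analysis plan that is not shown, and the list of baseline predictors is open-ended.

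**The model problem affects only supporting analyses, and a convergence fallback is ordinary analysis-plan content.** Both are true. Naming a link and covariate set likely to fail is still a choice made in this text.

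**Conclusion.** The point holds at modest size. The deciding analysis leaves out a factor used to stratify randomisation. If that factor is prognostic, the interval is roughly 1 to 14% too wide at q = 0.3 for gaps of 10 to 40 points, a loss of about 0.2 to 3 power points. This does not inflate the risk of falsely claiming non-inferiority and does not undermine the 138 per arm.

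The mixing of prevention with resolution matters more for interpretation, because it can dilute a difference among patients not constipated at entry: −15 pooled against about −21 in that group at q = 0.3. That is conditional on an assumed share and on the arms differing in that stratum only; the documents do not show that such dilution will occur. Stratifying the primary analysis does not cure it, since a stratified estimate still averages over both groups.

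The identity-link weakness is real but confined to the additional and weighted per-protocol analyses.

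**What to change.** 1. Make the primary analysis a risk difference stratified by baseline constipation, with Mantel-Haenszel weights and a stratified Newcombe interval, at the same -15% margin. Keep the unstratified Newcombe interval as a sensitivity analysis.
2. Prespecify the risk difference in patients with baseline BFI below 30 as a supporting estimate for the prevention claim.
3. In both the additional and the weighted per-protocol analyses, replace the identity-link binomial model by a logistic model standardised to a risk difference.

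**Cost:** plan wording and analysis code. Day-0 BFI is already collected, and no extra patients or visits are needed. The estimate in item 2 rests on fewer patients. With 30% constipated (assumed), about 0.7 × 138 ≈ 97 per arm remain, and the half-width is 1.96 × √(2 × 0.82 × 0.18/97) = 10.8 points if response in that stratum is 82%, or 9.1 points if it is 88%. It should therefore support the primary result, not decide it.
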